### Sample Size

The primary outcome of this study is the change in cognitive function as measured using the Beijing version of the Montreal Cognitive Assessment (MoCA). We prespecified a standardized between‑group effect size of *d*=0.40 on the MoCA at 8 weeks. This assumption is supported by a recent meta‑analysis of acupuncture for PSCI showing a pooled mean difference (MD) of 3.30 points (95% CI 2.19-4.40) versus control [36,37]. Using representative poststroke variability (MoCA score mean 21.1, SD 7.5), an MD of 3.30 corresponds to a standardized effect of approximately 0.44; thus *d*=0.40 is conservative. Therefore, the trial is powered on MoCA as the primary cognitive end point.

Using G Power (version 3.2.7) with a 2-tailed test, α set at.05 (type I error), and power (1 – β) at 0.80 (type II error β=.20), the minimum required sample size was calculated to be 44 participants (22 per group) [38]. To account for an anticipated 20% dropout or loss to follow-up rate, the total sample size was increased to 54 participants, with 27 participants allocated to each group.

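### At the plan's own 20% dropout rate, 54 randomised gives about 43 completers, just under the stated minimum of 44: a minor slip in the dropout step

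*Protocol article*

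**What the plan says.** The Sample Size section of the protocol article works in two steps. First, for a two-sided test at 0.05 with 80% power and a standardised effect of 0.40 on the MoCA at 8 weeks, "the minimum required sample size was calculated to be 44 participants (22 per group"). Second, the section enlarges that number for attrition: "To account for an anticipated 20% dropout or loss to follow-up rate, the total sample size was increased to 54 participants". Split equally, that is 27 per group. The section prints no formula for the enlargement.

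Study Design and Participants and Recruitment repeat 54 as the target, and Randomization and Allocation Concealment fixes a 1:1 ratio. Data Management says that missing outcomes will be multiply imputed under a missing-at-random assumption, with complete-case analysis as a sensitivity analysis.

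**The concern.** The enlargement exists so that, once the expected share of patients is lost, the stated minimum is still there. That can be checked by applying the 20% loss to the 54 randomised. The result falls below 44 in total and below 22 per group, so the sentence claims an allowance slightly larger than the one the number provides.

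What is at stake is mainly the accuracy of a stated design figure. There is also a practical reason to correct the method: an inflation that multiplies by 1.2 where it should divide by 0.80 loses little on a base of 44, but the loss grows in proportion to the base.

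**Working it through.** **Inputs, all from Sample Size unless noted**

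- Minimum evaluable: 44 in total, 22 per group
- Anticipated loss: 20%
- Randomised: 54 in total, 27 per group
- Allocation: 1:1 (Randomization and Allocation Concealment)
- Test: "with a 2-tailed test, α set at.05 (type I error"), with "power (1 – β) at 0.80 (type II error β=.20")
- Effect: "We prespecified a standardized between‑group effect size of *d*=0.40 on the MoCA at 8 weeks"

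**1. Reproducing the plan's 54**

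| Route | Calculation | Randomised total |
|---|---|---|
| Multiply per group by 1.20 | 22 × 1.2 = 26.4, up to 27; × 2 | 54 |
| Multiply total by 1.20 | 44 × 1.2 = 52.8, up to 53 | 53 (54 if made even) |
| Divide total by 0.80 | 44/0.80 | 55 |
| Divide per group by 0.80 | 22/0.80 = 27.5, up to 28; × 2 | 56 |

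Multiplication per group returns 54 exactly. Division returns 55 or 56.

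**2. Applying 20% loss to 54**

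- Total: 54 × 0.80 = 43.2, against 44, a gap of 0.8.
- Per group: 27 × 0.80 = 21.6, against 22, a gap of 0.4.
- At 56 randomised: 56 × 0.80 = 44.8, above 44.

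**3. The loss that 54 does cover**

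54 − 44 = 10 patients, and 10/54 = 18.5%. Per group this is 27 − 22 = 5, and 5/27 = 18.5%.

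**4. Effect on power (two-sample t test, two-sided 0.05)**

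- d = 0.40: 25.4% with 22 per group and 25.0% with 21.6 per group, a loss of 0.4 points.
- d of about 0.86, the effect for which 22 per group gives 80%: about 79% with 21.6 per group.

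**5. Chance of reaching the minimum**

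This assumes that each patient is lost independently with probability 0.20.

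| Randomised | At least 44 completers | At least 22 in both arms |
|---|---|---|
| 54 (27 per group) | 47% | 29% |
| 55 | 58% | not applicable (unequal arms) |
| 56 (28 per group) | 68% | 46% |

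**6. The base figure, for scale**

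With the stated d = 0.40, two-sided 0.05 and 80% power, the normal approximation gives 2 × (1.960 + 0.842)² / 0.40² = 98.1, so 99 per group. The t test gives 100 per group, or about 200 completers. Dividing by 0.80 gives 250 randomised; multiplying by 1.2 would give 240, ten short. The printed 44 therefore does not follow from its own inputs, and that discrepancy is far larger than the one examined here.

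**The case against.** The strongest reply is that the gap is too small to matter. It is less than one person, 54 covers 18.5% against a planning guess of 20%, and no decision changes. This stands as to weight: the effect on power is negligible. It does not make the sentence correct, because 54 does not deliver 44 at the rate the sentence names.

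A second reply is that completers are not the whole analysis set. Missing outcomes are to be multiply imputed, and Table 1 schedules a 4-week MoCA, so some patients who leave will contribute partial data. This stands in part. Counting each dropout as a full loss is a worst case, but imputation does not in general restore all the information lost with an outcome, and the complete-case sensitivity analysis depends directly on the completer count.

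A third reply is that the base of 44 is the real problem and that 54 will go when it is recalculated. That ranking is right. The inflation step still has to be done correctly then, when the same slip would cost ten patients.

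Four stronger readings are tempting, and the document does not support them:

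- *That the dropout protection is absent.* It is nearly complete: 54 absorbs 10 losses.
- *That the 47% and 29% in the working measure the damage.* Most of that risk comes from sizing on expected loss. A correctly inflated design would reach 44 with probability 58% at 55 randomised, and 22 in both arms with probability 46% at 28 per group. The slip accounts for about 11 and 17 percentage points respectively.
- *That the authors are known to have multiplied by 1.2.* The arithmetic fits, but no formula is printed.
- *That randomising 55 or 56 would repair the sample size.* It would not, because the base does not give the stated power.

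**Conclusion.** The point holds as a small and certain error. On the plan's own figures, 54 randomised with 20% loss leaves 43.2 expected completers (21.6 per group), against a stated minimum of 44 (22 per group). The shortfall is 0.8 of a completer, equivalent to 1 to 2 randomised patients, and costs about 0.4 points of power at d = 0.40.

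The conclusion takes the 20% as a share of those randomised and takes the 44 as printed, without endorsing it. It does not depend on how 54 was obtained. It should be ranked well below the separate failure of 44 to follow from the stated effect size and power.

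**What to change.** Correct the sentence in Sample Size in one of two ways:

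- state that 54 randomised allows for 10 losses (5 per group, 18.5%) from the minimum of 44; or
- keep the 20% and state that about 43 completers are expected from 54.

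When the base sample size or the power statement is corrected, inflate by dividing by (1 − dropout), round up within each group, and print the formula.

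The cost is one sentence and a slightly less favourable stated allowance. This point alone needs no added enrolment. The Results section reports that no participants have been enrolled as of August 2025, so the change can be made before any data exist. If the completer count is carried into a power figure at d = 0.40, that figure will be about 25%. That reflects the base calculation, not the dropout step, and belongs with the correction of the base.

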### Participants and Recruitment

We aim to enroll 54 participants through a combination of ward visits and online promotional efforts. Individuals expressing interest in participating will undergo eligibility assessment conducted through a screener, typically via contact at the recruitment office. A MoCA score of <26 is used as the primary cutoff to identify cognitive impairment in accordance with the standard diagnostic threshold recommended in clinical guidelines and previous studies. Patients scoring below this threshold are considered eligible for inclusion. In cases of low educational level (≤12 years), 1 point is added to the total MoCA score as per standard adjustment procedures. Should the applicant satisfy the research criteria, an invitation to partake in the study will be extended. Figure 1 shows the flow diagram of participants.

**Figure 1 figure1:**
[figure not shown]
Flow diagram of participants. DTI: diffusion tensor imaging; fMRI: functional magnetic resonance imaging; MBI: modified Barthel index; MMSE: Mini-Mental State Examination; MoCA: Montreal Cognitive Assessment; MOS SF-36: Medical Outcomes Study 36-Item Short-Form Health Survey; MRI: magnetic resonance imaging.

### Eligibility Criteria

Eligible participants must meet the specified inclusion criteria and not fall under the exclusion criteria. The inclusion criteria are as follows: confirmation of the diagnosis through adherence to the stipulated criteria and validation via head magnetic resonance imaging (MRI) or computed tomography examination; disease duration of >1 month; first ever stroke to avoid confounding effects of previous cerebrovascular events on brain network reorganization and cognitive function; conscious state with stable vital signs and nonprogressive symptoms; clear consciousness without meeting the criteria for *dementia* (Mini-Mental State Examination [MMSE] score of >17 for illiterate individuals, >20 for individuals with a primary school educational level, and >24 for individuals with a middle school educational level or higher—thresholds selected to ensure that participants can complete the full range of cognitive assessments while still presenting mild to moderate PSCI); onset of cognitive impairment after stroke; age of >18 years; right-handedness to reduce variability in brain lateralization patterns, which is particularly important for imaging analyses; and voluntary participation with the provision of self- or legal guardian–signed informed consent.

Exclusion criteria encompass recurrent disease; cognitive impairment originating from other causes; the presence of severe conditions such as liver, kidney, or heart disease; and impediments to cooperation with examinations due to severe hearing impairment, language barriers, or other significant reasons. In addition, all potential participants will be assessed using validated screening tools such as the Hospital Anxiety and Depression Scale or Hamilton Depression Rating Scale at baseline. Patients who meet the diagnostic threshold for moderate to severe depression or anxiety (Hospital Anxiety and Depression Scale score of ≥11 or Hamilton Depression Rating Scale score of ≥17) will be excluded from the trial to avoid emotional state confounding cognitive outcome assessments.

### Randomization and Allocation Concealment

An impartial statistician will generate a concealed random allocation sequence using the PLAN procedure in the SAS statistical software (version 9.1; SAS Institute). Eligible participants will be randomly assigned in a 1:1 ratio to either the acupuncture treatment group or the conventional treatment control group. The random sequence will be securely stored and managed by a project manager who is not involved in participant recruitment, screening, or outcome assessment. To ensure allocation concealment, the group assignments will not be disclosed to screeners, evaluators, or participants during the enrollment process. Once a participant is deemed eligible and enrolled, the project manager will inform them of their group assignment via telephone, thus maintaining strict separation between the randomization process and other trial operations.

Given the nature of acupuncture, it is not feasible to blind the practitioners delivering the intervention. We acknowledge that the lack of practitioner blinding could introduce performance bias and influence internal validity through potential nonspecific or placebo effects. To minimize these risks, we will (1) blind participants to the specific study hypotheses and expected effects of each intervention, (2) ensure that outcome assessors and statisticians remain blinded throughout the trial, (3) standardize the practitioner-patient interaction by using scripted instructions and limiting nonprotocol communication, and (4) provide the control group with conventional treatment to control for attention and treatment expectancy effects. These measures aim to reduce expectancy bias and placebo responses, thereby strengthening the internal validity of the trial despite the inherent limitations of acupuncture blinding.

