### Blinding

This study will use a single-blind design in which both the participants and the primary outcome assessors will remain blinded to group assignments. A designated project manager will oversee the generation of the randomization sequence and the allocation of blinding codes. Group assignments will be generated using a computer-based random number table and anonymized as group A or B.

Given the inherently distinguishable nature of acupuncture interventions, blinding of treating physicians is not feasible. However, all treating physicians will undergo standardized training to ensure consistent procedures and neutral communication, thereby minimizing observer bias.

Participants will be randomly assigned to either the acupuncture group or the conventional treatment group. To maintain participant-level blinding, the conventional treatment group will receive sham acupuncture using specially designed nonpenetrating needles applied to nonacupoint locations. The procedures, including manipulation, duration, and frequency, will be identical in both groups to ensure comparable treatment experiences.

Outcome assessors and statistical analysts will be blinded to the actual group identities and will only have access to anonymized labels (A or B). Conversely, treating physicians and project managers will not participate in outcome assessment or data analysis. Similarly, outcome assessors and analysts will not be involved in participant enrollment or allocation.

The blinding code will be securely sealed and will not be disclosed until the completion of all statistical analyses.

To assess the success of blinding, participants will be asked at the end of the treatment period to indicate which group they believe they were assigned to (A, B, or unsure) via a structured questionnaire.

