**Limitations and Future Directions**

While the randomized controlled trial and blinding methodologies are upheld, the feasibility of achieving total blindness has been acknowledged as challenging, particularly in nondrug trials. Given the unique nature of acupuncture treatment, a double-blind procedure is not feasible, leading to the decision to blind outcome evaluators and statistical analysts. In addition, both groups receive conventional cognitive training to ensure ethical equivalence; however, this may reduce the contrast between groups. Moreover, we acknowledge the limitations in generalizability of our study findings, primarily due to the single-center design and the constraints imposed by resource-intensive research protocols and the standardization of millimeter-level interventions. To minimize potential biases, we have implemented rigorous quality control measures. For future research, we plan to conduct multicenter trials to quantitatively assess general applicability and conduct additional real-world validation to further enhance the generalizability of our findings.

In summary, by adopting a multimodal neuroimaging approach, this study delves into the impact of acupuncture on the brain structure and function of patients with PSCI. By examining correlations with changes in cognitive function, this study aims to clarify the specific targets and mechanisms through which acupuncture enhances cognitive function. The findings are anticipated to yield reliable imaging markers for evaluating the efficacy of acupuncture and prognosis of PSCI, offering valuable clinical applications. If this study demonstrates a significant intervention effect, it will contribute robust evidence supporting acupuncture’s ability to ameliorate cognitive dysfunction in patients with PSCI, providing insights into its neuroimaging mechanisms.

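### The allocation procedure, read literally, tells each enrolled participant their group by telephone, which contradicts the Blinding section and would defeat the sham control

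*Protocol article*

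**What the plan says.** Three parts of the protocol article describe who knows the allocation.

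- **Randomization and Allocation Concealment.** The arms are named in clear: "Eligible participants will be randomly assigned in a 1:1 ratio to either the acupuncture treatment group or the conventional treatment control group". Concealment is limited in time: "the group assignments will not be disclosed to screeners, evaluators, or participants during the enrollment process". The next sentence begins "Once a participant is deemed eligible and enrolled" and continues that "the project manager will inform them of their group assignment via telephone". Among the safeguards listed later in the section, the one that concerns what participants know is to "blind participants to the specific study hypotheses and expected effects of each intervention".
- **Blinding.** Here "both the participants and the primary outcome assessors will remain blinded to group assignments". The sham has this as its stated purpose: "To maintain participant-level blinding, the conventional treatment group will receive sham acupuncture using specially designed nonpenetrating needles applied to nonacupoint locations". Assignments are recoded as A or B, the code stays sealed until every analysis is finished, and at the end of treatment participants are asked to guess A, B or unsure.
- **Limitations and Future Directions.** Double-blinding is called infeasible, "leading to the decision to blind outcome evaluators and statistical analysts". Participants are not mentioned in that list.

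**The concern.** The comparison is real against sham needling on a common background of rehabilitation and cognitive training. The Discussion (Brand New Insights) relies on the sham to tell the acupoint effect apart from a placebo response, and credits the group difference directly to acupoint stimulation. That inference requires participants not to know which needling they receive.

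If the arm is disclosed at allocation, the two groups can come to differ in expectancy, in effort on the cognitive tests, in retention, and in what participants let slip to assessors. The primary outcome, the MoCA, depends on effort, and the Discussion itself counts cognitive scales as subjective. The MMSE is exposed in the same way, and the SF-36 is self-reported. Blinded assessors do not remove a participant's own expectancy, and no analysis can restore blinding once the arm is known.

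**Working it through.** No figure in the plan bears on this point, so the check is a comparison of text.

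1. **Who receives the call?** The sentence opens with the enrolled participant, and the pronoun that follows has no other person to refer to. Treating physicians and acupuncturists are not mentioned in that paragraph.
2. **Does the concealment rule prevent it?** No. The rule covers the enrolment process only, and the call comes once enrolment is complete. Within that section, disclosure after enrolment is consistent with the rule.
3. **What is conveyed?** The group assignment. The only group names in that paragraph are the acupuncture treatment group and the conventional treatment control group. A participant told the second name, who then receives needling, could infer that the needling is sham. Coded labels do not appear in this section.
4. **When?** Table 1 puts randomization and allocation at week 0, and treatment runs for 8 weeks. A call made on enrolment and allocation would come before most or all of the treatment.
5. **What does the Blinding section require?** That participants do not know their group. The sealed code and the end-of-treatment guess both presuppose that they still do not know it when treatment ends.
6. **Can both be followed?** Not if the call names the arm: step 3 reveals what step 5 requires to be hidden.
7. **Does a coded label resolve it?** A call saying only A or B would not in itself reveal real or sham. But the protocol does not say that the call is coded, and where it restricts access to the coded labels it names outcome assessors and analysts, not participants. If participants had been given the label, the final question with answers A, B or unsure would ask them to repeat it. It would then measure recall and say nothing about whether blinding held.

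Under the literal reading blinding fails. Under the coded reading the blinding check fails. Under either, the text needs changing.

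**The case against.** The strongest reply is that this is a drafting conflict and not a decision to unblind. The Blinding section states the intent plainly and backs it with four provisions: nonpenetrating sham needles, A/B coding, a sealed code and an end-of-treatment guess. Against these stands one sentence whose pronoun may have been meant for the practitioner, or whose message may have been meant as a coded label. This part of the reply stands. The document contains two incompatible instructions and does not show which one staff would follow.

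A reader might therefore infer too much by concluding that every participant will certainly learn the arm before the first session. The documents do not support that, because the A/B coding and the sealed code leave the coded call open as an unstated possibility. A reader might also take the Limitations paragraph as evidence that participants were deliberately left unblinded. It does not say so: it names two blinded roles while explaining why double-blinding was ruled out, and the same paragraph says that blinding is upheld. It is a side note about an incomplete list.

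The reply does not rescue the sentence. The wording does not support a call to the practitioner, and the coded reading has to be supplied from outside the paragraph. Staff could follow the allocation section in good faith and disclose the arm.

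**Conclusion.** This is an internal contradiction that must be resolved before the first participant is allocated. It is not a design choice, since the Blinding section states the opposite intent. That the two sections conflict is certain. That blinding would actually be lost is conditional on the call naming the real arm, which is the literal reading.

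Under that reading the problem reaches all 54 planned participants, the primary outcome and the clinical secondary outcomes, and the group difference could no longer be credited to acupoint stimulation alone. The size of the bias cannot be derived from the document. Under the coded-label reading participants may stay blinded, but the planned check of blinding is uninformative.

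**What to change.** - In Randomization and Allocation Concealment, replace the telephone sentence: after enrolment the project manager releases the assignment only to the treating acupuncturist, and the participant is told neither the arm nor its A/B label.
- In Blinding, reword the end-of-treatment question so that the answers are real acupuncture, sham acupuncture or unsure. Once participants are no longer told a label, A and B mean nothing to them.
- Give the same list of blinded roles (participants, outcome assessors, statistical analysts) in Randomization and Allocation Concealment, in Blinding, and in Limitations and Future Directions.
- Check that what participants are told at consent agrees with this. The consent text was not available for this review.

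The cost is a few sentences and one reworded questionnaire item, with any written allocation instructions brought into line. The Ethical Considerations section routes significant protocol modifications through the ethics committee, so the change may need its approval. The Results section states that no participants had been enrolled as of August 2025; if that is still so, the problem can be prevented entirely.
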